#### 2.9.2. Health Related Physical Fitness Outcomes

All health-related physical fitness and body composition measurements will be conducted by trained research personnel following standardized testing procedures to ensure consistency and reliability of the measurements. Prior to data collection, assessors will receive training on the testing protocols and equipment use.

All assessments will be conducted indoors under controlled environmental conditions to minimize external influences on performance. To reduce potential confounding factors, participants will be instructed to avoid vigorous physical activity, caffeine intake, and heavy meals for at least two hours prior to testing.

To minimize fatigue effects and ensure consistency, the tests will be conducted in the following standardized order: body composition assessment, cardiorespiratory fitness test, muscular strength tests, muscular endurance tests, flexibility assessment. Adequate rest intervals of 3–5 min between tests will be provided to allow sufficient recovery and prevent fatigue from influencing subsequent test performance.

The study will generate preliminary estimates of intervention effects on several health-related physical fitness outcomes. Although the study is not powered to detect definitive intervention effects, the results will provide initial estimates of effect size that can inform sample size calculations for future large-scale randomized controlled trials.

*Body Composition Measurement*

Body mass index (BMI) will be calculated using the standard formula:$$\mathrm{BMI}\;=\;\frac{\mathrm{weight}\;(\mathrm{kg})}{{\mathrm{height}\;(m)}^{2}}$$

Participants’ height and body weight will be directly measured by trained researchers using standardized equipment, which will be used to compute BMI values. Height will be measured using an electronic stadiometer (iboga C8), while body weight will be measured using a body composition analyzer (InBody Dial H20N). BMI is widely applied in epidemiological studies as an indicator of weight status and has been shown to be strongly associated with total body fat [26]. Based on the calculated BMI values, participants will be categorized into four weight status groups: underweight (<18.5 kg/m^2^), normal weight (18.5–23.9 kg/m^2^), overweight (24–27.9 kg/m^2^), and obese (≥28 kg/m^2^).

In addition to BMI, body fat percentage and skeletal muscle mass will be assessed using a bioelectrical impedance analyzer (InBody H20, InBody Co., Ltd., Seoul, Republic of Korea). Prior to the assessment, participants will be instructed to remove all metal accessories, such as earrings, bracelets, and watches, to avoid potential interference with the electrical current used by the device.

Measurements will be performed when participants are in a normal physiological state, avoiding assessment immediately after food intake or vigorous physical activity. During the measurement procedure, participants will stand barefoot on the analyzer platform with both feet fully contacting the electrode plates. They will hold the device handles with arms relaxed at their sides to ensure proper contact between the fingers and electrodes, allowing accurate measurement of body composition parameters.

*Cardiorespiratory Fitness Assessment*

Cardiorespiratory fitness will be assessed using the Queen’s College Step Test, a validated and widely used submaximal field test for estimating maximal oxygen uptake (VO_2_max) in young adults [27]. The test is suitable for field-based studies due to its simplicity, safety, and minimal equipment requirements.

Participants will perform the step test on a 41.3 cm (16.25 inch) step bench for 3 min. The stepping cadence will be controlled using a metronome, set at 24 steps per minute for males and 22 steps per minute for females, following the standardized protocol. Participants will be instructed to maintain a consistent stepping rhythm using the sequence up–up–down–down throughout the test.

Immediately after completing the step test, participants will sit down, and their recovery heart rate will be measured between 5 and 20 s during the recovery period using a heart rate monitor. The recorded heart rate will then be converted to beats per minute (bpm) for analysis.

Estimated VO_2_max (ml·kg^−1^·min^−1^) will be calculated using the following standard prediction equations:

For males:VO_2_max = 111.33 − (0.42 × heart rate)

For females:VO_2_max = 65.81 − (0.1847 × heart rate)

Higher estimated VO_2_max values indicate greater cardiorespiratory fitness capacity.

*Muscular Strength Assessment*

Upper- and lower-body muscular strength will be assessed using one-repetition maximum (1RM) tests for the chest press and leg press, respectively. The 1RM test is a widely accepted method for evaluating maximal dynamic muscular strength and has demonstrated good reliability in healthy young adults [28]. Both tests will be conducted using fixed resistance machines, thereby minimizing movement instability and reducing the risk of exercise-related injury. Prior to formal testing, participants will attend a familiarization trial to practice the testing procedures and movement techniques. Participants will be screened for musculoskeletal contraindications before maximal strength testing. All tests will be supervised by trained personnel to ensure proper lifting technique and participant safety.

Before testing, participants will complete a standardized warm-up consisting of light aerobic activity followed by dynamic stretching to prepare the muscles for maximal effort.

For the chest press test, participants will perform the exercise using a resistance machine while maintaining proper body alignment and controlled movement technique. For the barbell back squat, participants will stand with feet shoulder-width apart and descend until the thighs are approximately parallel to the floor, while maintaining correct posture and spinal alignment.

The testing load will be progressively increased until the participant can complete only one repetition with proper technique, which will be recorded as the 1RM value. Participants will be given 3–5 min of rest between attempts to minimize fatigue. In most cases, the maximal strength value will be determined within three to five attempts.

If a participant fails to complete a repetition with proper technique, the load will be reduced following an adequate rest period and another attempt will be performed. The highest successfully lifted load (kg) will be recorded as the participant’s upper-body strength (chest press 1RM) and lower-body strength (squat 1RM).

*Muscular Endurance Assessment*

The Arm Hang Test measures upper-body muscular endurance by recording the duration (in seconds) that participants can maintain a chin-above-bar position while hanging from a horizontal bar with elbows flexed at approximately 90 degrees. Participants will be instructed to keep their body as still as possible during the test. Timing will begin once the participant assumes the correct position and will stop when the chin drops below the bar or when the participant can no longer maintain proper form.

Lower-body muscular endurance will be evaluated using the Wall Sit Test. Participants will lean against a wall and descend into a seated position with knees flexed at approximately 90 degrees and thighs parallel to the floor. Participants will be asked to maintain the position for as long as possible while keeping their back against the wall. The duration (in seconds) that participants can sustain the position without breaking form will be recorded. Longer durations in each test indicate greater muscular endurance capacity.

*Flexibility Assessment*

Flexibility will be assessed using the Sit-and-Reach Test, which evaluates the flexibility of the hamstring muscles and lower back [29].

Participants will sit on the floor with legs fully extended and knees kept straight, with the soles of their feet placed flat against the sit-and-reach box. With hands placed one on top of the other and arms extended forward, participants will slowly reach forward as far as possible along the measuring scale.

The distance reached (cm) will be recorded as the flexibility score, with greater reach distances indicating better flexibility. Each participant will perform the test twice, and the highest recorded value will be used for analysis.

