### 2.6. Randomization and Allocation

Eligible participants will be randomly assigned to one of three groups: Morning HIIT, Evening HIIT, or Control group, using a restricted lottery-based randomisation method with a 1:1:1 allocation ratio. To generate the allocation sequence, a total of 72 identical opaque sealed envelopes will be prepared, comprising 24 envelopes labelled “Morning HIIT”, 24 envelopes labelled “Evening HIIT”, and 24 envelopes labelled “Control”. The envelopes will be identical in size, colour, and appearance, and each allocation label will be folded and sealed inside the envelope so that the assignment cannot be seen before selection.

To ensure allocation concealment, the envelopes will be prepared and mixed by an independent researcher who is not involved in participant recruitment, baseline assessment, intervention delivery, or outcome assessment. The sealed envelopes will be placed in an opaque container and thoroughly mixed before the allocation process begins. Randomisation will be conducted only after eligibility confirmation, written informed consent, and completion of baseline assessments.

At the point of allocation, each participant will independently draw one sealed envelope from the opaque container under the supervision of a research team member. The selected envelope will then be opened to reveal the participant’s group assignment. Once selected, the envelope will not be returned to the container. This lottery procedure will be conducted without replacement until the required allocation of 24 participants per group is achieved. This process ensures that each participant’s allocation is concealed before assignment and is made independently and unpredictably upon enrolment.

Participants allocated to the Morning HIIT group will perform the training sessions in the morning, whereas participants allocated to the Evening HIIT group will perform identical training sessions in the evening. Participants allocated to the Control group will maintain their usual daily routines without participating in structured exercise during the study period. A schematic CONSORT diagram illustrating the intervention procedure is shown in Figure 2. Table 1 outlines the participant recruitment timeline, key milestones, and planned assessment activities.

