### 2.12. Statistical Analysis

All statistical analyses will be conducted using IBM SPSS Statistics version 27.0 (IBM Corp., Armonk, NY, USA). Descriptive statistics will be used to summarize participant characteristics, feasibility outcomes, and safety indicators. Continuous variables will be presented as means and standard deviations for normally distributed data, while medians and interquartile ranges will be reported for non-normally distributed data. Categorical variables will be presented as frequencies and percentages.

Prior to inferential analyses, the distribution of continuous variables will be assessed using the Shapiro–Wilk test and graphical inspection methods, including histograms and Q–Q plots. Homogeneity of variance and sphericity assumptions will also be evaluated where appropriate. Mauchly’s test of sphericity will be performed for repeated-measures analyses, and Greenhouse–Geisser corrections will be applied if the assumption of sphericity is violated.

As this study is designed as a feasibility pilot randomized controlled trial, analyses of intervention effects will be considered exploratory in nature. Therefore, greater emphasis will be placed on estimating effect sizes and confidence intervals rather than relying solely on statistical significance testing. Mixed designed ANOVA will be used to explore the effects of time (pre-intervention vs. post-intervention), group (morning HIIT, evening HIIT, and control), and time × group interactions on health-related physical fitness outcomes.

If substantial deviations from normality are observed, appropriate remedial approaches such as data transformation or robust statistical procedures will be considered. In addition, non-parametric analyses may be conducted as sensitivity analyses to evaluate the robustness of the findings.

Effect sizes will be calculated to provide preliminary estimates of intervention effects and to inform sample size estimation for future fully powered randomized controlled trials. Statistical significance will be set at *p* < 0.05. Where appropriate, intention-to-treat analyses will be performed to account for missing data and participant attrition.

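### The pooled VO2max effect size and SD depend on the sex mix, because heart rate is rescaled by sex and the stated model has no sex term

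*Protocol article*

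**What the plan says.** Section 2.9.2 (cardiorespiratory fitness) converts step-test recovery heart rate to a single outcome, estimated VO2max, which "will be calculated using the following standard prediction equations". For men the equation is "111.33 − (0.42 × heart rate"); for women it is "65.81 − (0.1847 × heart rate"). The stepping cadence also differs, being "set at 24 steps per minute for males and 22 steps per minute for females". The same section has recovery heart rate recorded in bpm.

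Section 2.6 allocates participants "using a restricted lottery-based randomisation method with a 1:1:1 allocation ratio". The only restriction is on arm totals, since envelopes are drawn "without replacement until the required allocation of 24 participants per group is achieved". Sex is not a stratum. Section 2.4 does not restrict eligibility by sex, and section 2.10 seeks sex balance only among interviewees.

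Section 2.12 states the model: "Mixed designed ANOVA will be used to explore the effects of time (pre-intervention vs. post-intervention"), together with group and the time × group interaction. No sex term is named. It treats the effect analyses as exploratory and stresses effect sizes and confidence intervals. Sections 2.9.2 and 2.12 both say that these effect sizes will inform the sample size of a later trial.

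**The concern.** Estimated VO2max is a linear rescaling of heart rate, with one scale for men and another for women. When both sexes are pooled in a model that does not know sex, an arm's mean change depends on how many men it holds as well as on the training response. The pooled SD likewise mixes two very different spreads.

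The trial's quantitative product for this outcome is an effect size to be carried forward. If that number moves with the sex mix, a later trial with a different mix inherits the wrong figure. A secondary worry is the morning-evening contrast. Both arms train, so both heart rates may fall, and a chance difference in the number of men would turn equal falls into unequal VO2max gains.

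**Working it through.** **Inputs from the protocol.** Slopes 0.42 and 0.1847, intercepts 111.33 and 65.81 (section 2.9.2). Arms of 24 (section 2.3), and 3 × 24 = 72 reproduces the stated total. The protocol gives no VO2max difference, SD or power to reproduce.

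**Assumptions, not in the protocol.** 36 men and 36 women; heart-rate SD 15 bpm; SD of heart-rate change 8 bpm, equal in both sexes; common falls of 0, 5 or 10 bpm.

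**1. Scale.** 0.42 / 0.1847 = 2.27. A 10 bpm fall gives 10 × 0.42 = 4.20 in men and 10 × 0.1847 = 1.85 in women. With male share p, the mean gain is 1.847 + 2.353p:
- p = 1/3: 2.63
- p = 1/2: 3.02
- p = 2/3: 3.42

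**2. SD of change.** Men: 8 × 0.42 = 3.36. Women: 8 × 0.1847 = 1.48. The variance ratio is 2.27² = 5.2.

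**3. Standardised effect** (10 bpm fall against no change in control).
- Within either sex the scale cancels: 4.20 / 3.36 = 1.847 / 1.478 = 1.25.
- Pooled 50:50, the within-sex variance is 64 × (0.42² + 0.1847²) / 2 = 6.74. The trained arm adds a between-sex part of (2.353 / 2)² = 1.38.
- Averaging the two arms' variances: √(6.74 + 1.38/2) = 2.73, so the standardised effect is 3.02 / 2.73 = 1.11.
- A trial sized on 1.11 instead of 1.25 needs (1.25 / 1.11)² ≈ 1.27 times as many participants.

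**4. SD of levels.** At the same heart rate men score higher by 14.9, 10.2 and 5.5 ml/kg/min at 130, 150 and 170 bpm. At 150 bpm the within-sex variance is 225 × (0.42² + 0.1847²) / 2 = 23.7. The sex gap adds (10.2 / 2)² ≈ 26.1. The SD rises from 4.9 to 7.1.

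**5. Chance imbalance.** With 36 men drawn into three arms of 24, the exact probability that morning and evening differ by at least 4 men is 32%, and by at least 5 men 20%.

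**6. Effect on the morning-evening contrast.** The sex offset cancels in pre-post change. What remains is 0.2353 × common fall × (gap in men / 24):
- no fall: 0
- 5 bpm, 4 men: 0.2353 × 5 × 4/24 = 0.20
- 10 bpm, 5 men: 0.2353 × 10 × 5/24 = 0.49

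The standard error of the contrast from within-sex variation is √(2 × 6.74 / 24) = 0.75, so even 0.49 is about 0.65 standard errors.

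**7. Over repeated randomisation.** Simulating the time × group test as an ANOVA on change, the mean arm difference is about 0. Type I error is 4.5–4.8% without a sex term and 4.3–4.7% with one. With men fixed at 15/9/12 and a 10 bpm fall in every arm, it is 6.0% without and 5.0% with. At a 10 bpm fall the standard error drops from about 0.82 to about 0.76 with a sex term; at no change there is no gain.

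**The case against.** The strongest reply is that nothing here is biased. Randomisation without stratification is valid, each participant's sex offset cancels in the change, and the test holds its nominal level. That stands. A reader might infer that sex imbalance alone manufactures an arm difference. It does not, because a shared heart-rate change is also needed and the resulting shift is under one standard error. Nor should the HIIT-versus-control pairs be counted as exposed in the same way, because the mechanism needs a similar fall in both arms.

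A second reply is that the equations may be right. If men truly gain more ml/kg/min per beat, an arm with more men really does gain more. That also stands: the protocol gives no ground for calling the equations an artefact. A later trial enrolling the same mix on the same pooled outcome would properly use the pooled SD. The difficulty is that the mix is neither fixed nor forecast.

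A third is that recovery heart rate is not a clean substitute. Men and women step at different cadences, so the workload differs by sex. Heart rate is therefore a useful companion to VO2max, not a sex-neutral replacement.

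Finally, the primary outcomes are feasibility indicators, the fitness analyses are exploratory, and a separate analysis plan might add covariates. This limits the weight of the point. Even so, the article itself states the outcome formula, the draw and the model effects, and as stated they fit together poorly.

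**Conclusion.** The point holds as a matter of interpretability and modest precision, not of bias. The pooled VO2max effect for one and the same 10 bpm fall runs from 1.85 to 4.20 ml/kg/min depending only on sex mix, and from 2.63 to 3.42 for male shares between one third and two thirds. This follows from the protocol's own slopes; only the size of the fall is assumed. Pooling also lowers the standardised effect from 1.25 to 1.11 under the stated assumptions.

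The possible shift in the morning-evening contrast is conditional on the draw: 0 without a heart-rate change, and about 0.2 to 0.5 ml/kg/min in the cases shown, against a standard error near 0.75. Sex mix, heart-rate level, SDs and change are all assumptions. A claim that the planned test is invalid, or that its error rate is inflated over randomisation, is not supported.

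**What to change.** In section 2.12, for VO2max and the other fitness outcomes, include sex and sex × time in the mixed ANOVA, or use ANCOVA on the post-intervention value with baseline and sex. A sex main effect alone in the pre-post ANOVA would leave the time × group estimate unchanged, so the interaction with time is the part that matters.

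Report recovery heart rate alongside VO2max with the same adjustment, and note the cadence difference. Show VO2max effect sizes and SDs separately for men and women, so that the next trial can be sized for its own mix.

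The cost is one or two degrees of freedom and some wording. Sex is already known, since cadence and equation depend on it, and heart rate is already recorded in bpm. Stratifying the envelope draw by sex is optional and possible only if allocation has not begun; Table 1 dates it to February–March 2026.

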### 2.10. Qualitative Interviews

Semi-structured interviews will be conducted with a subset of participants from the intervention groups to explore their perceptions and experiences regarding the HIIT module [30]. Semi-structured interviews allow participants to describe their experiences in depth while enabling the researchers to systematically explore key aspects of the intervention.

The interview questions will be developed based on previous qualitative research examining exercise intervention experiences [31]. The interview guide will focus on several core domains, including participants’ overall experiences with the intervention, perceived physical responses, psychological effects, perceptions of the training design, and suggestions for improving the programme. The detailed interview guide is presented in Table 3.

Participant recruitment for the interviews will follow the data saturation approach described by Francis [32]. Initially, 10 participants will be interviewed. Following the completion of these interviews, the data will be analysed to determine whether new themes continue to emerge. If additional themes are identified, three further interviews will be conducted. This process will continue in increments of three participants until no new themes emerge from the data, indicating that thematic saturation has been achieved.

To ensure a balanced representation of perspectives, the study will also aim to maintain gender balance among interview participants, targeting an approximate 1:1 male-to-female ratio. This approach is intended to account for potential gender-related differences in exercise perceptions and experiences [33].

Prior to the interviews, participants will be provided with clear information regarding the purpose of the study, interview procedures, and the intended use of the collected data. Written or verbal informed consent will be obtained before participation. Participants will also be informed that their participation is voluntary and that they may withdraw from the interview at any time without any negative consequences.

To ensure confidentiality and protect participant privacy, strict data protection procedures will be implemented. All interview recordings, transcripts, and related materials will be securely stored, and participants’ identities will be anonymized using unique identification codes rather than personal names.

### 2.11. Data Management

All participants will be assigned unique identification codes to ensure confidentiality. Personal identifying information will not be included in the analytical dataset. All data will be securely stored and accessible only to the research team.

### 2.12. Statistical Analysis

All statistical analyses will be conducted using IBM SPSS Statistics version 27.0 (IBM Corp., Armonk, NY, USA). Descriptive statistics will be used to summarize participant characteristics, feasibility outcomes, and safety indicators. Continuous variables will be presented as means and standard deviations for normally distributed data, while medians and interquartile ranges will be reported for non-normally distributed data. Categorical variables will be presented as frequencies and percentages.

Prior to inferential analyses, the distribution of continuous variables will be assessed using the Shapiro–Wilk test and graphical inspection methods, including histograms and Q–Q plots. Homogeneity of variance and sphericity assumptions will also be evaluated where appropriate. Mauchly’s test of sphericity will be performed for repeated-measures analyses, and Greenhouse–Geisser corrections will be applied if the assumption of sphericity is violated.

As this study is designed as a feasibility pilot randomized controlled trial, analyses of intervention effects will be considered exploratory in nature. Therefore, greater emphasis will be placed on estimating effect sizes and confidence intervals rather than relying solely on statistical significance testing. Mixed designed ANOVA will be used to explore the effects of time (pre-intervention vs. post-intervention), group (morning HIIT, evening HIIT, and control), and time × group interactions on health-related physical fitness outcomes.

If substantial deviations from normality are observed, appropriate remedial approaches such as data transformation or robust statistical procedures will be considered. In addition, non-parametric analyses may be conducted as sensitivity analyses to evaluate the robustness of the findings.

Effect sizes will be calculated to provide preliminary estimates of intervention effects and to inform sample size estimation for future fully powered randomized controlled trials. Statistical significance will be set at *p* < 0.05. Where appropriate, intention-to-treat analyses will be performed to account for missing data and participant attrition.

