To address this research gap, the present study developed a structured HIIT module specifically designed for Chinese college students. Before implementing large-scale intervention programmes, it is essential to evaluate the feasibility and practicality of the training module within the target population. Feasibility studies play a critical role in the early stages of intervention development by assessing recruitment, adherence, acceptability, and implementation challenges within real-world contexts [14]. In addition to quantitative assessments of health-related physical fitness outcomes, qualitative methods such as semi-structured interviews can provide valuable insights into participants’ experiences, perceived benefits, and potential barriers related to the intervention.

Therefore, the present study aims to evaluate the feasibility and preliminary effect of an eight-week time-specific high-intensity interval training (Chrono-HIIT) programme among low-physically active Chinese college students with an intermediate chronotype. The primary objective of this feasibility pilot randomized controlled trial is to assess the practicality and acceptability of implementing the intervention, including participant recruitment, retention, adherence, safety, and data completeness. The secondary objective is to explore the preliminary effects of morning versus evening HIIT on health-related physical fitness outcomes, including body composition, cardiorespiratory fitness, muscular strength, muscular endurance, and flexibility. In addition, the qualitative component of the study aims to explore participants’ experiences, perceived benefits, barriers to participation, and overall acceptability of the intervention. It is hypothesized that the Chrono-HIIT programme will demonstrate acceptable feasibility and adherence among low-physically active Chinese college students and may produce preliminary improvements in health-related physical fitness outcomes. The findings may contribute to the optimization of physical education programmes and inform the design of future large-scale randomized controlled trials aimed at promoting efficient and sustainable physical activity interventions in college settings.

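### The effects named for the mixed ANOVA do not isolate morning versus evening, and a baseline-adjusted model would estimate that contrast more precisely

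*Protocol article*

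**What the plan says.** The secondary objective in section 1 of the protocol article is to "explore the preliminary effects of morning versus evening HIIT on health-related physical fitness outcomes".

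For these outcomes section 2.12 names one model, with two time points and three arms: "Mixed designed ANOVA will be used to explore the effects of time (pre-intervention vs. post-intervention), group (morning HIIT, evening HIIT, and control"). The third effect listed is the time-by-group interaction. The section names no pairwise contrast and no baseline covariate.

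It also says how the results will be used. The analyses are exploratory and "greater emphasis will be placed on estimating effect sizes and confidence intervals rather than relying solely on statistical significance testing". Effect sizes are to be calculated "to inform sample size estimation for future fully powered randomized controlled trials", without saying which effect size.

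Two design facts matter here. Section 2.3 plans 24 participants per arm, 72 in all. Sections 2.1 and 2.6 place randomisation after the baseline assessments.

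**The concern.** The objective is a two-arm comparison, but each effect named in section 2.12 answers a different question.

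- The time effect pools all three arms, including the untreated controls.
- The group effect averages the pre-randomisation visit with the post-intervention visit, so it dilutes any treatment effect.
- The interaction has two degrees of freedom and combines HIIT versus control with morning versus evening.

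A pilot that stresses estimates and intervals needs a named single-degree-of-freedom contrast, because an omnibus term has no single difference to put an interval around. An effect size attached to the interaction also cannot size a later morning-versus-evening trial.

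The second issue is precision. With two visits, pairwise comparisons from this model are differences in mean change. When baseline is measured before randomisation, conditioning on it gives a narrower interval from the same data. With 24 per arm that is worth having.

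**Working it through.** **Inputs.** From the documents: 24 per arm and three arms (section 2.3), two time points (section 2.12), baseline before randomisation (section 2.6), and a 0.05 significance level (section 2.12; two-sided assumed). Not in the documents, so assumed: the pre-post correlation rho, shown over a range; equal SDs at the two visits; the same rho in each arm. Differences are in SD units.

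**The plan's own figure.** 3 × 24 = 72 reproduces. No SD, effect size or power is stated, so there is no power calculation to reproduce.

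**Step 1: what the interaction is.** With two visits, the time-by-group F equals the one-way ANOVA F on change scores. On one simulated data set both were 4.1311 on 2 and 69 df. In the same fit, the evening-minus-morning interaction coefficient equalled the difference in mean change (-0.335 both ways). The model therefore contains the wanted contrast, but as a change-score comparison.

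**Step 2: what the named effects measure.** Suppose both HIIT arms exceed control by d after the intervention and timing has no effect.

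- Group effect, HIIT arm minus control: (0 + d)/2. With d = 0.75 this is 0.375; simulation gave 0.376, 0.374 and 0.381 at rho 0.5, 0.7 and 0.9.
- Interaction: the three arm means (d, d, 0) have sum of squares 2d²/3 about their average, so the noncentrality is n(2d²/3) / [2(1-rho)]. With d = 0.5, n = 24 and rho = 0.7 this is 24 × 0.1667 / 0.6 = 6.67. Cohen's f is the square root of 6.67/72, or 0.30, although the timing effect is exactly zero. The interaction is then significant in 61% of trials (40% at rho 0.5, 80% at rho 0.8).

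So neither the interaction test nor its effect size carries specific information about timing.

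**Step 3: precision of the morning-versus-evening contrast.**

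- Change score: variance = 2σ²(1-rho) × (2/n)
- Baseline-adjusted: variance = σ²(1-rho²) × (2/n)
- Ratio: (1-rho²) / [2(1-rho)] = (1+rho)/2

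The half-widths below use t on 69 df for change scores, and t on 68 df with a small-sample penalty for the covariate after adjustment. For example, at rho 0.5 the change-score half-width is 1.995 × 1 × √(2/24) = 0.576.

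| Assumed rho | Variance ratio | 95% CI half-width, change score | 95% CI half-width, adjusted |
|---|---|---|---|
| 0.3 | 0.65 | 0.681 | 0.554 |
| 0.5 | 0.75 | 0.576 | 0.503 |
| 0.7 | 0.85 | 0.446 | 0.414 |
| 0.8 | 0.90 | 0.364 | 0.348 |
| 0.9 | 0.95 | 0.258 | 0.253 |
| 0.95 | 0.975 | 0.182 | 0.181 |
| 0.98 | 0.99 | 0.115 | 0.115 |

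Simulation (4,000 trials per rho) gave variance ratios of 0.757, 0.857 and 0.965 at rho 0.5, 0.7 and 0.9. At rho 0.5, 24 × 0.75 = 18 per arm with adjustment matches 24 per arm without it. With 20 completers per arm at rho 0.5, the half-width goes from 0.63 to 0.55.

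**The case against.** The strongest reply is that the model does estimate what is wanted. Morning minus evening in change is a contrast of the fitted interaction, section 2.12 promises effect sizes and confidence intervals, and an article may leave the list of contrasts to a fuller plan that is not shown. This stands. A reader might infer that the mixed ANOVA cannot deliver the secondary objective; step 1 shows that it can. The omission of the contrast is therefore a modest point. The choice of model is different, because section 2.12 states it. A fuller plan that only added pairwise contrasts to that model would keep the less precise estimator.

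A reader might also take the 40% to 80% figures as false-positive rates. They are not. They are the power of the omnibus test to detect a real HIIT effect, which is itself of interest, and nothing in section 2.12 says that a significant interaction would be read as a timing effect. Nor does the section say that the main effects would be read as treatment effects, or that the omnibus effect size would be the one carried forward. It leaves that open.

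It is also true that change scores are unbiased under randomisation, and that the gain rests on a rho that the document does not give. BMI and body composition may correlate highly over eight weeks, and for such outcomes little would be gained.

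Finally, a reader might want sex in the model, because the step-test cadence is "set at 24 steps per minute for males and 22 steps per minute for females" and the VO2max equations have slopes of 0.42 and 0.1847 (ratio 2.27). This does not support the remedy. Change scores already remove stable sex differences in level, and an additive sex term does not correct unequal slopes in the prediction equations.

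**Conclusion.** The point holds as one of specification and efficiency. The effects named in section 2.12 do not isolate the comparison in the secondary objective, and the contrast that the model can supply is less precise than a baseline-adjusted one from the same measurements.

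The size depends on rho. The interval is about 19% narrower at rho 0.3 (0.554/0.681 = 0.81), 13% at 0.5 (0.503/0.576 = 0.87), 7% at 0.7 (0.414/0.446 = 0.93) and 2% at 0.9 (0.253/0.258 = 0.98). Above about 0.95 the gain is negligible, and at 0.98 the cost of the covariate cancels it. These figures assume equal SDs at the two visits and a common rho.

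The planned analysis is not invalid. It concerns exploratory secondary outcomes in a trial that does not claim power for them.

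**What to change.** In section 2.12, replace the mixed ANOVA for each fitness outcome with a linear model of the post-intervention value on arm and the baseline value of the same outcome. Name three contrasts, each with a 95% confidence interval: evening minus morning, identified as the secondary objective; morning minus control; and evening minus control. State that these pairwise estimates, and not the omnibus interaction effect size, will inform the sample size of the future trial.

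The cost is one model degree of freedom (68 instead of 69 residual df with 72 participants) and a change of wording. It needs no new data, because both visits are already planned.
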